**Statistical Analyses**

Basic statistical analyses will be performed as described in the diagnostic study. We will evaluate 18 known predictors (i.e. *age; sex; clinical features* (NIHSS or GCS), *important comorbidities* (coronary artery disease, heart failure, atrial fibrillation, hypertension on admission, previous TIA/Stroke, renal disease, dementia, diabetes); *location of the lesion* (LACS etc.); *stroke subtype by the TOAST criteria*; *therapies* (thrombolysis); *laboratory parameters (*baseline glucose level on admission [46-50], CRP); *body temperature*; *smoking histo*ry), and copeptin levels in our multivariate analysis. All variables will first be tested one by one against the dependent variable unfavorable outcome (defined either as Barthel index <85 or modified Ranking scale 3 to 6) for the presence of a significant association. Only variables significantly associated with the outcome will be assessed in a multivariate model performed separately for each parameter.

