**Inclusion criteria**

1. All consecutive patients who are admitted to the emergency department with an ischemic or hemorrhagic stroke or transient ischemic attach (TIA) according to the World Health organization criteria [37] with symptom onset within the last 3 days.

2. All consecutive patients who undergo intracranial surgery due to

- pituitary tumors

- intracerebral hemorrhage (ICH)

- subarachnoidal hemorrhage (SAH)

- chronic subdural hematoma

- head trauma with contusio cerebri

- intracranial abcesses

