**Exclusion criteria**

Patients without informed consent.

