**C Procedures**

**Baseline data collection (Appendix 6)**

Access to data of all eligible patients that are not included into this study is important to avoid a selection bias. Thus, we will collect baseline data and information on inclusion and exclusion criteria in all eligible patients irrespective whether they are or are not included into the study. This will allow the comparison of baseline data of eligible patients who consented to participate with those who did not.

Baseline data collection in patients will be collected by the investigators and contain

a) age

b) gender

c) BMI

d) Medical history items: actual history that preceded the hospitalization; ABCD score in patients with transient ischemic attack (Rothwell [38]**Appendix 7**); family history; relevant co-morbidities also assessed by the charlson index [39] (**Appendix 8**) (i.e. hypertension, previous stroke, previous TIA, ischemic heart disease, atrial fibrillation, diabetes mellitus, renal and liver dysfunction, congestive heart failure, dyslipidemia; comorbidities with the risk of hyponatremia (severe hypothyroidism, glucocorticoid insufficiency, neoplasm, HIV infection); smoking history (pack-years) and status (pack per day); current medication; alcohol consumption (glass and grams per day); time from onset of symptoms to admission.

e) Place of residence: i.e. independent living, defined as living at home or in an old people’s home with or without support of the family circle and/or professional care (the family circle consists of the spouse and/or other important persons who live together with the patient; dependent living, defined as nursing home long-stay department, other hospital [40].

f) Clinical items: physical examination including neurological status, NIHSS (to assess the severity of stroke in stroke patients) and Glasgow Coma scale (GCS [41]); blood pressure, pulse rate, weight, volume status (including skin turgor, jugular venous distension, auscultation, if available flow sheet of fluid intake and loss), body temperature; in neurosurgical patients intracerebral pressure if performed within the routine clinical management.

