**Management of participants throughout the trial**

Step 1. All eligible patients in the emergency department or the neurological ward or the neurosurgical ward will be included into the study.

Step 2. All baseline data will be collected.

Step 3. During hospitalization we Clinical items including weight, blood pressure, pulse rate, volume status and body temperature will be assessed by chart review until discharge. In neurosurgical patients, we will monitor intracerebral pressure if performed within the routine clinical management.

- Fluid treatment and drugs

- Potential symptoms of hyponatremia, i.e. headache, nausea, vomiting, muscle cramps and aches, anorexia, impaired consciousness, seizure **(Appendix13)** [9].

- Routinely performed laboratory tests (chemogramm, plasma glucose, serum osmolality, urine osmolality, sodium in urine, hematocrit) will be sampled at the time-points when blood sampling is routinely done on the wards.

Step 4. In all patients, on day 5 of the hospitalization, a clinical examination with GCS, NIHSS, Barthel Index and Ranking Scale will be performed.

The future place of residence (i.e. dependent vs. independent living) will be assessed.

Step 6. In patients with ischemic stroke a telephone follow-up **(Appendix 14)** regarding morbidity and mortality (as assessed by the Barthel Index and Ranking Scale) will be obtained after 3 months. An unfavorable outcome will be defined as a Barthel index <85 or modified Rankin scale of 3 to 6 [43].

Patients after neurosurgery will have a telephone follow-up **( Appendix 15)** after 3 months to evaluate mortality, relapse, and quality of life as assessed by the Glasgow outcome scale [44] and Barthel index.

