**E. Sample Size considerations**

Design

This is a prospective observational study to evaluate Copeptin as a diagnostic and prognostic marker in neurological and neurosurgical patients.

Analysis

Analysis tools

All relevant clinical and laboratory parameters obtained by interview, clinical tests and reviewing of the medical records will be entered into an Excel® database. Statistical Analysis System (SAS® Institute, Cary, NC, USA) and R for Windows (R Foundation for Statistical Computing, www.r-project.org) will be used for data analysis. Statistical evaluation will include stepwise logistic regression analysis to assess which variables are independently associated with outcome.

Sample size considerations

Our sample size consideration is based on our intention to determine an optimal clinical model to predict the outcome of neurological and neurosurgical patients (based on Barthel index, Rankin scale NIHSS scale and Glasgow outcome scale) (i.e. the prognostic question of the study). To determine an optimal clinical model we will undertake a multivariable regression analysis. It has been demonstrated that multiple regression models with a minimum of 10 to 15 observations per predictor variable reveal good estimates [45]. We will evaluate 18 known predictors (i.e. *age; sex; clinical features* (NIHSS or GCS), *important comorbidities* (coronary artery disease, heart failure, atrial fibrillation, hypertension on admission, previous TIA/Stroke, renal disease, dementia, diabetes); *location of the lesion* (LACS etc.); *stroke subtype by the TOAST criteria*; *therapies* (thrombolysis); *laboratory parameters (*baseline glucose level on admission [46-50], CRP); *body temperature*; *smoking histo*ry) in our multivariate analysis. Therefore, we aim to include a minimum sample size of 180 patients (for 10 observations per predictor) to 270 (for 15 observations per predictor) and a maximum sample size of 360 patients (for 20 observations per predictor). All variables will first be tested one by one against the dependent variable unfavorable outcome (defined either as Barthel index <85 or modified Ranking scale 3 to 6) for the presence of a significant association. Only variables significantly associated with the outcome will be assessed in a multivariate model performed separately for each parameter.

Based on the last year’s data in our hospital, the following number of patients with stroke and neurosurgery will be eligible:

*Patients*

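### The 18 listed predictors include no pre-admission function, although the outcome is an absolute level of function that some enrolled patients may already meet and place of residence is collected

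*Protocol*

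**What the plan says.** **Outcome.** Under Management of participants throughout the trial (Step 6), the protocol states for stroke patients: "An unfavorable outcome will be defined as a Barthel index <85 or modified Rankin scale of 3 to 6 [43". Section E makes this the dependent variable of the prognostic model; each candidate is "tested one by one against the dependent variable unfavorable outcome (defined either as Barthel index <85 or modified Ranking scale 3 to 6"). It is a level of function at follow-up, not a change from the state before the event.

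**Who enters.** The first inclusion criterion reads "All consecutive patients who are admitted to the emergency department with an ischemic or hemorrhagic stroke", extended to TIA. The only exclusion is "Patients without informed consent". Neither restricts prior function.

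**What is collected.** Baseline item e is "Place of residence: i.e. independent living, defined as living at home". Residential homes for the elderly fall in the same category, and the help a person receives there does not alter it: the category applies "with or without support of the family circle and/or professional care". The other category is "dependent living, defined as nursing home long-stay department, other hospital [40". The baseline list printed in the protocol has no pre-admission Rankin or Barthel score. In the text, both scales are first applied on day 5. The baseline form (Appendix 6) is not shown.

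**What is modelled.** Both the Statistical Analyses text of 2.2.2 and section E say "We will evaluate 18 known predictors" and enumerate them. Residence and prior function are not among them. Only variables significant one by one go forward, and section E adds stepwise selection.

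**The concern.** A patient already at Rankin 3 or worse, or at Barthel below 85, before admission will usually be classed as unfavorable at 3 months however the new stroke evolves. For such a patient the outcome largely records prior status.

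The protocol presents copeptin as a reflection of the acute stress response, and section E looks for variables independently associated with outcome. If copeptin is higher in previously dependent patients for reasons that the model does not capture, part of its apparent association would come from marking old disability. What is at stake is the claim of independent association. The description of who does badly at 3 months is not in question.

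This is not a detail left to a later analysis plan. The predictor list is printed in full, twice, and the sample size is built on its length.

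**Working it through.** **1. The plan's own count and sample size.** Age (1), sex (1), NIHSS or GCS (1), comorbidities (8), lesion location (1), TOAST subtype (1), thrombolysis (1), glucose and CRP (2), body temperature (1), smoking (1): 1+1+1+8+1+1+1+2+1+1 = 18. Then 18 × 10 = 180, 18 × 15 = 270 and 18 × 20 = 360, as stated. Feasible number: 480 × 0.80 × 0.90 = 345.6, which agrees with the stated figure of about 350. None of the 18 is residence or prior function. The nearest proxies are age, dementia and previous TIA/stroke.

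**2. How many events could come from previously dependent patients.** Ischemic stroke patients with follow-up: 300 × 0.80 × 0.90 = 216. The protocol gives neither the proportion dependent before admission (d) nor the overall unfavorable proportion (o), so both are assumed. If all previously dependent patients end unfavorable, their share of events is d / o:

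| d (assumed) | patients, 216 × d | o = 30% (64.8 events) | o = 40% (86.4) | o = 50% (108) |
|---|---|---|---|---|
| 5% | 10.8 | 16.7% | 12.5% | 10% |
| 10% | 21.6 | 33.3% | 25% | 20% |
| 20% | 43.2 | 66.7% | 50% | 40% |

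This share is not itself a bias in copeptin. Bias also needs copeptin to differ by prior dependence.

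**3. When bias arises.** Logistic simulations with n = 216 and no true copeptin effect, all other inputs assumed, separate the cases. Percentages are false-positive rates for copeptin at a nominal 5%.

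- *Copeptin does not differ by prior dependence* (adjusted for severity only; 97% of dependent patients unfavorable): 4.2% at d = 10% and 5.5% at d = 20%. There is no inflation.
- *Copeptin differs only through listed covariates* (age, renal disease, heart failure and CRP drive both copeptin and dependence, dementia also drives dependence; 95% of dependent and 30% of other patients unfavorable; copeptin 0.44 to 0.47 SD higher in the dependent). Adjusted for these five: odds ratio 1.00, with 6% at d = 10% and 5% at d = 19%. The inflation essentially disappears.
- *Copeptin differs by a route outside the listed covariates* (0.3 to 0.5 SD higher in the dependent; adjusted for severity, age, dementia and previous stroke): 8 to 11% at d = 10% and 13 to 28% at d = 20%. With a prior-dependence term added: 3.5 to 5%.

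The third case is a condition, not an estimate. Nothing in the protocol shows that it applies.

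**4. Whether the listed covariates are sure to be in the model.** They are not. A covariate that misses significance in the one-by-one screen is not carried forward, and stepwise selection can remove others. The protection in the second case therefore depends on a step that the protocol leaves to the data.

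**5. Sample size after adding one term.** 19 × 10 = 190, 19 × 15 = 285, 19 × 20 = 380. If copeptin, which 2.2.2 names in addition to the 18, is counted as well: 20 × 10 = 200, 20 × 15 = 300, 20 × 20 = 400. The 10- and 15-per-predictor targets stay below about 350. The 20-per-predictor target exceeds it, but so does the existing 360.

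**The case against.** The strongest reply is that the likely reasons for a copeptin difference are already in the model: age, renal disease, heart failure, and infection through CRP and body temperature. The second case in the working bears this out. It stands as long as those covariates are retained and there is no further route from prior dependence to copeptin. The protocol secures neither.

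A second reply is that the protocol wants an optimal clinical model for prediction, and functional state at 3 months is a legitimate endpoint for that in all comers. This also stands. It limits the point to the independent-association claim. In addition, mortality, ICU stay and length of hospitalization are outcomes that no patient has met before admission.

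Stronger readings are tempting and should be resisted:

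- A reader might infer a several-fold false-positive rate for copeptin. Figures of that kind come from unadjusted or severity-only models with assumed inputs. They do not describe the multivariable model that the protocol plans.
- A reader might infer that prior function is never recorded. The printed baseline list has no such score, but Appendix 6 is not shown, and residence, the preceding history and the Charlson index are collected.
- A reader might infer that the whole risk-stratification question is confounded. For pure prediction it is not.

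**Conclusion.** The point holds in a limited form. The text establishes an absolute outcome, enrolment without regard to prior function, and a closed list of 18 predictors that omits a relevant baseline item already being collected. Whether this distorts copeptin's adjusted association depends on a copeptin difference by prior dependence beyond the listed covariates, or on loss of those covariates in selection. The protocol gives no figure for either, so no size can be assigned. With no copeptin difference there is no bias. The illustrative figures in the working rest on assumed dependence rates, outcome rates and copeptin shifts. The change is worth making because it is nearly free and because prior function is harder to recover after baseline.

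**What to change.** 1. Add pre-admission place of residence to the predictors in 2.2.2 (Statistical Analyses) and section E, and keep it in the model whatever the univariable screen or stepwise step shows. This changes wording only; the data are already collected.
2. Preferably, ask the patient or a relative one baseline question giving a pre-admission Rankin grade, and use that grade as the covariate. Residence is coarse because someone living at home with professional care is classed as independent. If Appendix 6 already records such a score, only the predictor list needs changing.
3. Report copeptin's association also in patients who were independent before admission.

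The cost is one more model term, with the sample-size consequences shown in the working, and one short question.

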**Measurement of copeptin concentrations**

Copeptin levels will be measured with a new chemiluminescens sandwich immunoassay with a lower detection limit of the assay of 0.4 pmol/L. Therefore, we will sample an additional 7.5ml Plasma EDTA tube which is asserved during the respective routine blood samplings. No additional blood sampling will be done.

**D. Potential risks, Adverse events and Monitoring board**

We consider the risks of this study to be minor and limited to the following

Blood Loss: 7.5ml of EDTA-plasma will be additionally drawn during each routine blood sampling. The total additional blood loss for this study will be less than 50 ml.

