#### 1. SYNOPSIS

**Background:**

Sodium imbalance is common and an adverse prognostic factor in hospitalized patients. However, identifying the causes of sodium imbalance is challenging in clinical practice. Levels of antidiuretic hormone (ADH) are elevated in patients with stroke correlating with disease severity and stress level; however, its measurement is cumbersome. ADH is derived from a larger precursor peptide along with Copeptin, which is a more stable peptide directly mirroring the production of ADH. Copeptin can be assayed readily in plasma. Early prognostic factors to predict in-hospital mortality and medium/long-term outcome in critically ill neurological patients, are helpful to guide and tailor early decisions on treatment, discharge from the intensive care unit and application of interventions to prevent deterioration of neurological functions.

**Aim:** To evaluate Copeptin as a diagnostic tool in disturbances of water homeostasis and prognostic tool to predict outcome in a well-defined cohort of stroke patients and patients undergoing intracranial surgery.

**Design:** Prospective, observational study.

**Location Setting:** Emergency and neurogical and neurosurgical clinic of the University Hospital of Basel.

**Patients:** Neurological patients with ischemic and hemorrhagic stroke and patients undergoing intracranial surgery.

**Intervention:** After informed consent, all routinely determined baseline data will be assessed including medical history, clinical items (i.e. neurological status, volume status, pulse rate, blood pressure, weight) and laboratory items (i.e. urine / serum osmolality, electrolytes, among others). All patients will have a follow-up with clinical and laboratory assessment until the day of discharge. After 3 months, they will be followed-up by a structured telephone interview to assess outcome (mortality, morbidity, as assessed by the ranking scale and Barthel index). Copeptin will be assessed in a batch analysis upon completion of the plasma asseveration.

**Variables and measurements:** Baseline data on medical history and clinical items, co-morbidities and treatment procedures will be collected. This exploratory study will be conducted over a 12 month period from November 2006 to November 2007.

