**Statistical Analyses**

Copeptin levels will be assessed in a blinded batch analysis upon completion of the plasma asseveration.

Discrete variables will be expressed as counts (percentage) and continuous variables as means ± standard deviation (SD) or median (interquartile range), unless stated otherwise. First, the overall prevalence of hyponatraemia in neurological and neurosurgical patients will be assessed. Frequency comparison will be done by chi-square test. Two-group comparison of normally distributed data will be performed by Students t-test. For multigroup comparisons, one-way analysis of variance with least square difference for posthoc comparison will be applied. For data not normally distributed, the Mann-Whitney-U test is used if only two groups are compared. The Kruskal-Wallis one-way analysis of variance with Bonferroni’s multiple posthoc test will be used if more than two groups were being compared.

Furthermore we will do a correlation analysis of copeptin levels with sodium levels, serum osmolality and other diagnostic laboratory parameters. Correlation analyses will be performed by using Spearman rank correlation. Levels that are non-detectable will be assigned a value equal to the lower limit of detection for the assay. All testing will be two-tailed and P values less than 0.05 were considered to indicate statistical significance. Scatterplot data will be shown with GraphPad Prism®, Version 4.00 for Windows (GraphPad Software, San Diego California, USA).

We will then compare the diagnostic accuracy of Copeptin levels with other potential biomarkers for sodium imbalance, e.g. atrial natriuretic peptide (ANP) and B-type natriuretic peptide (BNP). The ability of Copeptin to foresee sodium disbalance before it becomes evident by laboratory analysis will be assessed. Therefore we will correlate Copeptin levels with sodium level changes over time.We will construct receiver operating characteristic (ROC) curves and determine the areas under the receiver operating characteristic curve (AUC). The sensitivity and specificity to predict the correct diagnosis of hyponatraemia will be determined, based on the above standardized algorithm [32]. This ascertainment will be done retrospectively on the basis of the review of the complete patient charts by two study investigators, blinded to each other’s diagnosis. Discordant cases will be mutually discussed and resolved. Patients will be managed as usual according to the state of the art treatment.

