**Informed consent statement (Appendix 9 a and b,10,11,12)**

The study will be approved by the ethics committee of Basel (Ethikkommission beider Basel). It is important to note that this is an exploratory and observational study; the only study related intervention will be the asseveration of 7.5ml of plasma obtained during the routinely performed blood sampling. Therefore, patients are required to provide written informed consent that they agree for the use of their data for scientific purposes. In patients, in which “informed consent” is not feasible due to sequela of the acute CNS lesion (the latter a prerequisite for inclusion), patients’ next to kin can sign an assent form to state the presumptive will of the patient. In case, next of kin are not readily available, a treating physician – who must not be involved in the study – have to certify that there are no objections for inclusion in the study from his point of view. Only after these informed consent procedures the patient can be included in the study.

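### A 7.5 ml study tube at each routine draw, with no maximum number, keeps the stated total blood loss below 50 ml only up to the sixth draw

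*Protocol*

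**What the plan says.** Section D of the Protocol names blood loss as the study's risk and gives the rule and the total in consecutive sentences: 7.5 ml of EDTA plasma "will be additionally drawn during each routine blood sampling. The total additional blood loss for this study will be less than 50 ml". The total carries no condition, so it reads as applying to every patient.

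The section on measurement of copeptin concentrations gives the same rule in the plural: "we will sample an additional 7.5ml Plasma EDTA tube which is asserved during the respective routine blood samplings". It adds that there is no separate blood sampling for the study.

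Two other places determine how many draws there can be. The Synopsis (Intervention paragraph) states: "All patients will have a follow-up with clinical and laboratory assessment until the day of discharge". The section on management of participants says that routine laboratory tests "will be sampled at the time-points when blood sampling is routinely done on the wards". Neither gives a number of draws or a maximum number of study tubes.

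The informed consent statement says that "the only study related intervention will be the asseveration of 7.5ml of plasma obtained during the routinely performed blood sampling". It gives no number of repetitions and no total.

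Repeated copeptin values are needed. The statistical analyses of the diagnostic study aim to see whether copeptin foresees a sodium disturbance before it shows in the laboratory: "Therefore we will correlate Copeptin levels with sodium level changes over time".

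**The concern.** A rule with no upper limit on draws is paired with a fixed ceiling on volume. The ceiling can be guaranteed only if the number of draws is bounded, and the protocol does not bound it.

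Long stays are foreseen. Prolonged ICU stay and length of hospitalization are outcomes in neurosurgical patients, and the inclusion criteria admit intracerebral and subarachnoid hemorrhage, head trauma with contusion and intracranial abscess. These are the patients in whom many routine draws are most plausible.

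Two things are at stake. First, blood loss is the only risk to which the protocol attaches a figure, and that figure may be too low for some patients. Second, the number and timing of copeptin measurements, the index test of the study, are not fixed. The consent section does not settle either point. A reader cannot tell from it whether 7.5 ml is the amount per draw or for the whole study.

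**Working it through.** **Inputs**

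- Volume per draw: 7.5 ml (section D; section on measurement of copeptin concentrations).
- Stated ceiling: less than 50 ml (section D).
- Number of routine draws, k: not stated.
- Length of stay: not stated. Laboratory assessment runs to discharge (Synopsis), and all patients are to be examined on day 5 (management of participants).

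**The plan's own figure.** The total of less than 50 ml cannot be reproduced, because no k is given. The check is therefore for which k it is true.

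Total = 7.5 × k, and 50 / 7.5 = 6.67, so the total is below 50 ml for k ≤ 6 and above it for k ≥ 7.

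| Draws k | Total (ml) | Below 50 ml? |
| --- | --- | --- |
| 1 | 7.5 | yes |
| 5 | 37.5 | yes |
| 6 | 45.0 | yes |
| 7 | 52.5 | no |
| 10 | 75.0 | no |
| 14 | 105.0 | no |

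**From draws to days (assumption; the protocol gives no frequency).** With one routine draw a day from day 1, a patient has given 5 × 7.5 = 37.5 ml by day 5, within the limit, and passes it on day 7. With one draw every second day from day 1, the seventh draw falls on day 1 + 2 × 6 = 13. The day of a breach thus depends strongly on ward practice, whereas the seventh draw as threshold does not.

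**Plasma or blood.** The copeptin section speaks of a 7.5 ml tube, which makes 7.5 ml the blood volume. The consent statement and section D speak of 7.5 ml of plasma. If that were meant literally, the blood needed per draw would be 7.5 / (1 − haematocrit). The haematocrit is an assumption, shown over a range:

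| Haematocrit | Blood per draw (ml) | After 4 draws (ml) | After 5 draws (ml) |
| --- | --- | --- | --- |
| 0.35 | 11.5 | 46.2 | 57.7 |
| 0.40 | 12.5 | 50.0 | 62.5 |
| 0.45 | 13.6 | 54.5 | 68.2 |
| 0.50 | 15.0 | 60.0 | 75.0 |

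On that less natural reading the limit is reached or passed at the fourth or fifth draw. The main result uses the tube volume.

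**The case against.** The strongest reply is that the two sentences in section D do not contradict each other. Both are true for any patient with six or fewer routine draws, and with a daily draw a patient at day 5 is still within the limit. The ceiling could also be meant as the working limit, and the plural in the copeptin section need not cover every ward draw. No extra venepuncture is made, and no estimate, endpoint or sample size depends on the 50 ml figure.

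Much of this stands. A reader might infer that the sampling rule and the ceiling can never hold together; the documents do not support that, because a breach needs a seventh draw and the draw frequency is unstated. What the reply does not remove is that section D says each routine draw, sets no cap and states the total for everyone. If the ceiling is the limit, nothing says which draws are to be skipped.

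A reader might also take the consent statement as promising a single tube. It does not say so and can be read as the amount per sampling; it is ambiguous rather than contradictory. The consent forms are appendices not available here, so what patients are told cannot be judged.

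Finally, one might infer that copeptin will be selectively missing in late-onset or long-stay cases, biasing the diagnostic comparison. That would follow only if tubes stopped after one draw or when the limit was reached. The protocol states neither rule. As written, a tube is taken at every draw and none is lost.

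**Conclusion.** The point holds as a gap between an uncapped sampling rule and an unconditional total. At the tube volume of 7.5 ml, the total is assured up to six draws (45 ml) and exceeded from the seventh (52.5 ml). That threshold uses only the protocol's own figures. The expectation that some patients will pass it rests on the case mix and on length of stay being an outcome; how many, and by how much, cannot be derived. The 75 ml and 105 ml totals describe stays of 10 and 14 days only if one draw a day is assumed.

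The consent statement should be brought into line because it is silent on repetition and total, not because it is shown to be wrong. The mixed use of plasma and tube is a wording fault that could matter if taken literally.

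Severity is minor to moderate: the only quantified risk needs correcting and the sampling of the index test needs fixing, but no analysis result is shown to be biased.

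**What to change.** Reconcile section D, the section on measurement of copeptin concentrations and the informed consent statement in one of two ways:

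1. **Cap the tubes.** State a maximum of six study tubes per patient, 6 × 7.5 = 45 ml of blood, and name the sampling times. Choose them so that serial values remain for the planned analysis of copeptin against later sodium changes, including values before a disturbance appears.
2. **Keep a tube at every routine draw.** Restate the total blood loss in section D so that it fits the number of draws expected, or give it per draw with a realistic upper figure for long stays.

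In either case give the same repetition and total in the informed consent statement, check the consent forms against it, and describe the sample throughout as a 7.5 ml EDTA blood tube rather than as plasma.

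The cost is a wording change and, for the first option, a tube checklist. The cap also loses some late serial copeptin values in long-stay patients; the second option avoids that loss but requires a higher stated blood loss. Which draws to use within a cap is for the investigators to decide; reserving tubes until sodium is already abnormal could weaken the aim of detecting a disturbance beforehand.
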